## Abstract

**Introduction:**

Depression and fatigue are common in breast cancer survivors, and their presence is associated with personal suffering and worse prognosis. While many women receive short-term psychological support in the acute treatment phase, this is rarely available in subsequent phases. Internet interventions for breast cancer survivors could provide additional psychological support, as they are easily accessible and may be effective. However, no trial has yet examined the effectiveness of an Internet intervention that provides cognitive behavioural therapy techniques plus lifestyle advice for this population. This trial aims to test whether *Optimune*, a novel Internet intervention we developed for that purpose, leads to improvements in quality of life and relevant lifestyle habits over the course of 3 to 6 months.

**Methods:**

This randomized controlled trial (RCT) will include 360 female breast cancer survivors who have completed the active tumour eradication phase. Participants will be recruited from various settings, including web-based advertisements and Internet forums in German-speaking countries. The main inclusion criteria are a breast cancer diagnosis less than 5 years ago and completion of acute treatment at least 1 month ago, as verified by discharge letter from an oncology treatment centre. Participants will be randomly assigned to either (1) a control group, in which they receive care as usual (CAU) and are given access to *Optimune* after a delay of 3 months (CAU/wait list control), or (2) a treatment group that may also use CAU and will receive 12-month access to *Optimune* immediately after randomization. The three primary endpoints are quality of life, physical activity and diet quality, assessed with the World Health Organization Quality of Life Questionnaire, the International Physical Activity Questionnaire and the Food Quality Questionnaire, at 3 months post-baseline; secondary outcomes include cancer-related fatigue, emotional stress, depression, anxiety, fear of progression, insomnia, usefulness of the programme and negative treatment effects. Online assessments are conducted at baseline (T0), 3 months (T1) and 6 months (T2).

**Discussion:**

Results of this RCT are expected to extend the body of knowledge with regard to the effectiveness of CBT-based Internet interventions for female breast cancer survivors.

**Trial registration:**

ClinicalTrials.gov, NCT03643640. Registered on 23 August 2018.

## Background

Approximately 70,000 women are diagnosed with breast cancer in Germany annually [1]. Breast cancer is the most frequent cancer among women worldwide, with an incidence of 2.09 million women each year [2]. The German guidelines for the treatment of breast cancer [3] delineate several acute treatment options, including surgery, radiation and aggressive combination chemotherapy. When these treatments are completed and patients are considered cancer-free, they are typically discharged from a phase of intense treatment to a phase of standardized monitoring for recurrence, with only a few specific therapies, such as treatment with antihormones, aromatase inhibitors or bisphosphonates.

While many women receive short-term psychological support in the phase of acute treatment, this is rarely the case in subsequent phases. Although women successfully treated for breast cancer often do not experience cancer recurrence during the monitoring phase, they frequently experience other symptoms. For example, an average of 27% of breast cancer survivors experience clinically significant fatigue following treatment [4, 5]. Furthermore, 40% of breast cancer survivors are affected by depression and 27% by anxiety, on average, and these symptoms typically persist for more than 5 years after diagnosis [6, 7]. There is also evidence that breast cancer survivors have higher levels of inflammation [8–10], which may contribute to their commonly elevated levels of depression, fatigue and anxiety [8, 9, 11].

Several pharmacological depression treatments have been shown to be effective among breast cancer survivors. A systematic review reported that the prescription of antidepressants is more common among breast cancer survivors (average rate of 23%) compared to other cancer types, even though some controversy persists as to whether selective serotonin re-uptake inhibitors interact with tamoxifen [12, 13]. Certain serotonin re-uptake inhibitors may alleviate depression, in part because of their effects on cytokines such as interleukin-6 (IL-6) and tumour necrosis factor (TNF)-α, whereas other antidepressants do not appear to reduce cytokine levels [14]. Of note, several studies showed improvement of depressive symptoms after administration of antiphlogistic agents, including nonsteroidal anti-inflammatory drugs (NSAIDs) and cytokine inhibitors [15, 16], suggesting a causative link between depressive symptoms and pro-inflammatory cytokines.

Certain psychological interventions for depression, including mindfulness-based stress reduction (MBSR), cognitive behavioural therapy (CBT) and supportive-expressive dynamic psychotherapy have also been shown to have an impact on inflammatory markers (e.g. IL-6, TNF-α) in several psychiatric and somatic diseases with comorbid depression [17–19]. A recent meta-analysis suggested that mindfulness meditation has an effect on inflammatory biomarkers such as C-reactive protein (CRP) or nuclear factor kappa-light-chain-enhancer of activated B cells (NF-ĸB) but seems neutral for a variety of other cytokines [20]. Moreover, a randomized controlled trial (RCT) with a sample of breast cancer survivors showed that yoga reduced fatigue and inflammation and showed a trend for the reduction of depressive symptoms [21]. Several other studies among cancer survivors have also shown that psychological interventions, including CBT and mindfulness-based treatment, may enhance quality of life as well as reduce pro-inflammatory signalling [22–24].

Even though CBT and perhaps other forms of psychotherapy are promising treatments for depression among breast cancer survivors, these psychological treatments are not always available [25]. Psycho-oncological services that offer such treatments are in short supply in Germany and elsewhere, particularly in rural areas [26]. Furthermore, various individual and systemic barriers may prevent breast cancer survivors from accessing psychological treatments, including stigma concerns, scepticism regarding psychotherapy, time constraints, disease-related restrictions, lack of motivation and perceived lack of necessity [27].

A potential barrier to pharmacological depression treatment is that physicians are often reluctant to prescribe antidepressants because of concerns over side effects or drug-drug interactions [12]. According to the German guidelines for psycho-oncology, psychotherapy as well as antidepressants are recommended for the treatment of depression in breast cancer survivors [28]. This recommendation is consistent with guidelines in several other countries, such as the USA and UK [29, 30]. To improve access and extend the range of available psychological treatment options for breast cancer survivors, Internet-based psychological interventions could play an important role [25, 31].

Given the potential utility of effective digital interventions, our team has developed a novel Internet-based intervention termed *Optimune*. This individually tailored Internet intervention targets female breast cancer survivors and was developed by Gaia, a German research-focused small-to-medium enterprise (SME) with more than 10 years of experience in the development of similar interventions. For example, 12 RCTs have demonstrated the efficacy of *Deprexis*, an Internet intervention for depression developed by the same team with the same technology [32–43]. A recent meta-analysis yielded an effect size of *g* = 0.54 for *Deprexis* [44]. Other evidence-based interventions developed by this group target anxiety disorders, fatigue in multiple sclerosis and harmful drinking as well as depression and anxiety in epilepsy [34, 45–47]. *Optimune* aims to reduce distress, depression, anxiety and, in particular, chronic inflammation in breast cancer survivors (see the Methods/design section for the intervention description).

The goal of this pragmatic RCT [48] is to test the effectiveness of this novel Internet intervention on improvements in quality of life and relevant lifestyle parameters (dietary and exercise habits) among breast cancer survivors over a period of 3 months, in comparison to a control group that only receives access to the intervention after 3 months. Both groups are free to utilize other treatments that may be required; thus, *Optimune* will be offered adjunctively to care as usual (CAU). Because control group participants can access *Optimune* after 3 months, they are on a wait list (WL) only with respect to the Internet intervention. Thus, the control group is best characterized as CAU/WL. It is hypothesized that, at 3 months post-baseline, participants randomized to the intervention group will report higher levels of quality of life, physical activity and diet quality compared to participants randomized to the CAU/WL control condition. In order to examine stability of intervention effects over time, data will also be collected at 6 months. Additional analyses will examine a broad range of secondary outcomes, including cancer-related fatigue, stress, depression, anxiety, fear of cancer progression and insomnia. The subjective usefulness of the intervention will also be examined. Exploratory analyses will be conducted to examine potential negative intervention effects.

## Methods/design

### Study design

In this parallel-group RCT, participants will be randomized to two groups: (1) a control group, in which they may engage with any treatment and receive access to the Internet intervention after a delay of 3 months (CAU/WL), or (2) a treatment group that immediately receives access to the Internet intervention and may also use CAU (see Fig. 1). The trial aims to maximize external validity by examining the effect of adding a self-management intervention to the realities of current clinical care; it does not aim to maximize internal validity by selecting a maximally homogeneous patient group that does not reflect the clinical reality outside of trials [49]. Participants will be recruited consecutively from various sources, with every woman having an equal chance of being assigned to the intervention or control group (no block randomization). Given the pragmatic design, participants are not blinded to group assignment. Randomization will be performed by the Principal Investigator (PI), using a computer-generated sequence to generate the allocation sequence. However, the PI will not have any access to any participant data prior to performing the randomization. The other researchers who do have access to participant data in order to clarify inclusion/exclusion criteria will not have access to the randomization sequence. Thus, concealed allocation will be ensured.

**Fig. 1 Fig1:**
[figure not shown]
Flowchart of the study design

The content and design of this RCT are in accordance with the guidelines for clinical trial protocols as specified by the Standard Protocol Items: Recommendations for Interventional Trials (SPIRIT) 2013 statement [50]. The SPIRIT checklist is provided as Additional file 2. Moreover, this RCT is registered at ClinicalTrials.gov (NCT03643640), and any changes to this protocol will be described in this trial registry. The trial will conform to methodological standards recommended by the Consolidated Standards of Reporting Trials (CONSORT) statement [51].

### Recruitment and assessment

Study participants will be recruited via different channels. First, the study will be advertised online, and interested participants will be informed via Google ads, Internet forums and a dedicated Facebook page. Furthermore, treatment centres will be informed about the goals and procedures of the study and provided with informational material such as flyers and posters. Other recruitment channels will include patient associations, support groups and health insurance companies. Women who are interested in participating will be referred to the study homepage [52]. Internet users who use search engines such as Google with certain search terms (e.g. breast cancer self-help, breast cancer study, *Optimune*, etc.) will be shown a short ad that refers to the study homepage; potential participants may also be referred to the study homepage via other means (e.g. a recommendation by their treating oncologist/gynaecologist or their health insurance company). On the study homepage, interested participants will be invited to sign up with their name and e-mail address. A member of the research team will then contact potential participants by e-mail in order to invite them to the online baseline assessment (T0). Prior to completing the online baseline measures, further study information will be presented and online informed consent will be obtained.

After providing consent and completing the T0 online assessment, eligible participants will be asked to verify their diagnosis and therapies by providing the research team with a discharge letter from their oncology treatment centre or clinic. After receipt of this and confirmation of all inclusion/exclusion criteria, eligible participants will be randomized. One member of the study team will monitor registration for the programme and contact the participants if they do not sign up within 1 week after access to the intervention has been granted. Participants will be contacted again after 3 months (T1) and 6 months (T2) to complete the respective online assessments (see Table 1), and they will be reminded up to two times if they do not respond to the initial invitations. Previous studies evaluating similar interventions have shown that effects on psychosocial outcomes can be observed after a relatively brief period of 8 to 12 weeks [34, 36, 40–43, 46]. To evaluate the stability of effects and to allow the examination of potential effects beyond the 3 months time point, online assessments will also be conducted for both groups 6 months post-randomization.

**Table 1 Tab1:**
[figure not shown]
Study interventions, measures and measurement points

*WHOQOL-BREF* World Health Organization Quality of Life Questionnaire, *IPAQ* International Physical Activity Questionnaire, *FQQ* Food Quality Questionnaire, *BFI-9* Brief Fatigue Inventory, *IES-R* Impact of Event Scale-Revised, *PHQ-9* Patient Health Questionnaire, 9 items, *GAD-7* Generalized Anxiety Disorder 7-item questionnaire, *PAF-12* Fear of Progression Questionnaire, *ISI* Insomnia Severity Index

^a^Only for intervention group

^b^For each group: 15 days after access was granted

### Inclusion criteria

Women will be included if they have received a breast cancer diagnosis less than 5 years ago and acute treatment for breast cancer (such as surgery, chemotherapy or radiation treatment) has been completed at least 1 month prior to study entry. Prophylactic treatment with antihormone therapy such as tamoxifen, aromatase inhibitors or bisphosphonates is permitted. Eligible participants must be between 30 and 70 years of age; provide informed consent; be competent in the German language; and be willing to provide the discharge letter to verify their diagnoses and therapies.

### Intervention

*Optimune* is an Internet intervention for female breast cancer survivors. The intervention was developed by a multidisciplinary team of clinical psychologists, CBT therapists, physicians, software engineers, graphic artists and professional speakers, among others, who are affiliated with Gaia in Hamburg, Germany. Beyond established CBT techniques targeting depression, anxiety and fatigue, this intervention engages users in therapeutic techniques that have been shown to have beneficial effects on immune system functioning and inflammation, including sleep and stress management (e.g. mindfulness-based techniques) and lifestyle change (dietary and physical activity advice). The dimensions addressed in the programme are consistent with the German treatment guidelines for breast cancer survivors [28, 53].

The development team strove to include only techniques that are supported by evidence, and relevant citations are provided throughout the programme, accompanied by brief summaries of the respective journal article or book (annotated bibliography). Overall, 240 citations are provided across all *Optimune* modules. Content is continuously automatically adapted via software algorithms in order to match users’ individual preferences, concerns and needs. Content is conveyed in the format of interactive ‘simulated dialogues’ in which users read information or listen to recordings and then select one of several pre-programmed response options. The intervention uses a responsive web-design approach and can be accessed on a password-protected, secure (https-encrypted) website via any computer or smartphone. Illustrations, audio recordings and optional daily text messages with motivational content accompany the programme (see Additional file 1 for screenshots).

Throughout the development process, breast cancer survivors were continuously involved to test preliminary versions and provide feedback to ensure the quality of the software, consistent with development guidelines [54]. Expert feedback was sought from several physicians specializing in the treatment of patients with breast cancer, and the literature on CBT for breast cancer survivors was reviewed [24, 55, 56]. Like other software programs developed by this group, the intervention was produced on a proprietary software (broca®) developed by Gaia. The software-based intervention uses cloud computing with fast global access and is securely hosted in an ISO-27001-certified data centre located in Germany.

The *Optimune* intervention can be accessed over a period of 1 year. Depending on factors such as reading speed, preference for greater or lesser depth and desire to listen to audio recordings, each module can be completed in approximately 30–45 min. It would be possible to work through the entire intervention in as little as approximately 6 h. As in other interventions developed by our group [34, 39, 40], there is no fixed or generic sequence in which modules must be completed, nor is there a minimum number of sessions that must be finished. Users are invited to freely explore the intervention and let themselves be guided within each section by the algorithm-driven sequences that the intervention generates. Users are also informed that they can discontinue the intervention at any time if they feel that it is not helpful or may even be harmful.

The *Optimune* intervention comprises 16 modules that cover four broad domains: (1) psychological well-being, (2) dietary coaching, (3) exercise and physical activity coaching and (4) sleep management. An introductory module provides the user with an overview of the purpose, functions and time frame of the intervention. Participants are engaged in interactive sequences in which the role of inflammation and the immune system in breast cancer are briefly explained. The introductory module further addresses topics such as current emotional well-being (including possible symptoms of stress, depression and anxiety) as well as exercise and dietary habits. Participants are provided with a summary (’personal profile’) of their responses, and they receive initial personalized recommendations. Furthermore, participants are encouraged to complete each new module once it is activated for them, and to allow sufficient time between sessions to work on the tasks and exercises introduced in each session. They are informed that intervention access is provided for a 12-month period. The four intervention domains are outlined in the following subsections.

#### Psychological well-being

This domain provides an interactive overview of the role positive and negative emotions may play in inflammation and immune system functioning, and it introduces individually tailored exercises to reduce stress and improve well-being. Mindfulness and mental imagery exercises (including audio recordings) are introduced and practiced, and concepts/techniques such as activity scheduling, behavioural activation and basic psychological need satisfaction are introduced. Similar to the modules in the other domains (other than the introductory module), every module in this domain begins with a brief review of tasks that were assigned in the previous module.

#### Dietary coaching

Participants are provided with a brief overview of nutrition and dietary habits in the context of inflammation. The technique of stimulus control is introduced, and participants are encouraged to reduce the availability of potentially pro-inflammatory foods (e.g. heavily processed foods, crisps, pizza, doughnuts, cake, red meat, lemonade) from the household and restock with ’anti-inflammatory foods’ (e.g. primarily certain vegetables and fruits, such as blueberry, raspberry, broccoli, spinach, avocado, olive oil, turmeric). As in all other modules, evidence-based behaviour-change techniques such as goal setting, action planning and mental contrasting (of pros and cons or goal obstacles and solutions) are used.

#### Exercise/physical activity coaching

The first module within this domain starts with a personalized exploration of current exercise and physical activity habits, followed by an interactive review of relevant research findings and their implications for daily life. Participants are encouraged to set realistic and attainable exercise goals for the coming weeks and use prompts/reminders to facilitate the adoption of new exercise habits. Mental imagery exercises and other behaviour-change techniques are used (e.g. case examples to encourage modelling, identifying barriers and problem solving, agreeing on behavioural contracts, reviewing if-then plans, action-planning and rehearsing implementation intentions and using positive mental imagery and self-motivational statements).

#### Sleep management

This domain begins with an interactive exploration of current sleep quality and potential difficulties (insomnia symptoms and impairment in quality of life). Psychoeducational content regarding the importance of sleep for immune system functioning is provided, followed by an interactive exploration of evidence-based CBT techniques for overcoming insomnia (sleep hygiene, establishing regular sleep-wake rhythms, etc.). A personalized plan with suggestions for healthy sleep habits is provided, and users are encouraged to apply the presented techniques in order to optimize their sleep quality in the coming weeks.

### Outcome measurements

All outcome measures will be used in their German version and assessed via a secure, encrypted online survey service. Participants will be invited via e-mail to complete the online self-report questionnaires. If they do not respond to the initial invitation, a member of the research team will send them up to two reminder e-mails.

### Primary outcomes

Three equally important primary endpoints are defined: quality of life, dietary quality and physical exercise. Differences in change from baseline between study groups at 90 days from randomization will be assessed with the World Health Organization Quality of Life Questionnaire (WHOQOL-BREF), the International Physical Activity Questionnaire (IPAQ) and the Food Quality Questionnaire (FQQ). Success of the trial is defined as demonstrating a significant intervention effect on at least one of these endpoints. Given that multiple outcomes increase the familywise error rate, Bonferroni’s adjustment will be used [57].

Quality of life will be measured using the World Health Organization’s *WHOQOL-BREF*, which is a shorter version of the original instrument. The WHOQOL-BREF [58, 59] is a 26-item, 5-point rating scale with good to excellent psychometric properties (reliability and validity [60]). It measures the following domains: physical health, psychological health, social relationships and environment. Response options range from 1, indicating ’very dissatisfied’, to 5, indicating ’very satisfied’ and relate to the last 2 weeks.

Physical activity will be measured using the short version of the *International Physical Activity Questionnaire (IPAQ-SF)*. The short version of the IPAQ is a 7-item questionnaire that assesses the types of intensity of people’s physical activity and sitting time performed during their daily lives. Open-ended questions surrounding individuals’ last 7-day recall of physical activity are considered to estimate total physical activity (minutes/week) and time spent sitting. The IPAQ-SF has been evaluated as an acceptable measure to assess activity or fitness, as shown in a systematic review [61]. Overall, its reliability is acceptable to good.

Diet quality will be measured using the *FQQ*. The FQQ is a newly developed short food frequency questionnaire which includes 10 food items on a 5-point rating scale. It focuses on fruit, vegetables, high-sugar foods, processed food, meat and drinks. The aim of the tool is to measure diet quality. Response options range from 0, indicating ’daily’, to 3, indicating ’once or never’. A global diet quality score can be obtained by averaging all the items on the FQQ. This questionnaire is based on other, similar questionnaires, and its psychometric properties are being evaluated for the first time in this study.

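### The Food Quality Questionnaire score is inconsistently defined: a 5-point scale is coded 0 to 3, and one coding is averaged over foods to be eaten more and foods to be eaten less, with no item direction stated

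*Protocol article*

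**What the plan says.** All of the scoring text is in the Protocol article, Primary outcomes.

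- Status of the endpoint: "Three equally important primary endpoints are defined: quality of life, dietary quality and physical exercise". The success rule is "Success of the trial is defined as demonstrating a significant intervention effect on at least one of these endpoints".
- Format: a questionnaire "which includes 10 food items on a 5-point rating scale".
- Coding: "Response options range from 0, indicating ’daily’, to 3, indicating ’once or never".
- Content: "It focuses on fruit, vegetables, high-sugar foods, processed food, meat and drinks".
- Scoring: "A global diet quality score can be obtained by averaging all the items on the FQQ".
- Validation: the tool is new, and "its psychometric properties are being evaluated for the first time in this study".

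Two other places bear on it. The Dietary coaching section shows that the programme wants some of these foods cut (for example heavily processed food, cake, red meat) and others, mainly vegetables and fruit, eaten instead. The Background hypothesises higher diet quality in the intervention group at 3 months.

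**The concern.** There are two separate problems in the same paragraph.

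First, the number of response options contradicts itself. A scale coded 0 to 3 in whole steps has four options; a 5-point scale that starts at 0 would run to 4. One statement is wrong, so the possible range of a primary endpoint is not known from the text.

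Second, the coding and the scoring rule do not fit the content. Under the printed codes, a higher number means the food was eaten less often, whatever the food. That is an improvement for sugar, processed food and meat, and a deterioration for fruit and vegetables. A plain mean adds the two together. An intervention that achieves both of its dietary aims would push the mean up with one set of items and down with the other.

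At stake is whether the endpoint can show a real dietary benefit at the planned sample size, and whether its sign can be read. For an established instrument a published manual would settle the keying. Here the article cites no scoring source for the FQQ and says that it is new.

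**Working it through.** **Plan's own figure first.** Sample size calculation and analysis gives d = 0.35, power 0.80, alpha 0.05/3 = 0.0167 and total N = 346. A two-sided two-sample t-test (noncentral t) needs 173 per group, so 346, with power 0.802. The figure reproduces and is not affected by this point. At the recruitment target of 180 per group, power is 0.82.

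**Number of options.** Codes 0, 1, 2, 3 make four options. Codes 0, 1, 2, 3, 4 make five.

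**Direction of the mean.** Let h be the number of the 10 items on foods to be eaten more often. If every item improves by one category, a consistently keyed mean changes by 1.0. Without recoding, h items fall by 1 and 10 − h rise by 1, so the mean changes by (10 − 2h)/10:

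- h = 2: +0.6
- h = 3: +0.4
- h = 4: +0.2
- h = 5: 0
- h = 6: −0.2

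**Standardised effect and power.** Assumptions, none of them in the article: 10 items of unit variance, common correlation c = 0 to 0.3 after correct keying, the same shift δ on every item, and a correctly keyed effect of d = 0.35, borrowed from the sample size section.

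1. Keyed total: variance 10 + 90c, so δ = 0.35 × √(10 + 90c) / 10. This is 0.1107 at c = 0 and 0.2129 at c = 0.3.
2. Unrecoded total, with k = 10 − 2h: mean shift kδ, variance 10 + c(k² − 10).
3. d(unrecoded) = kδ / √(10 + c(k² − 10)).
4. Example, h = 2 (k = 6): at c = 0, 6 × 0.1107 / √10 = 0.21; at c = 0.3, 6 × 0.2129 / √17.8 = 0.30.
5. Power: two-sided t-test, alpha 0.0167, 180 per group, noncentrality d × √90.

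| Eat-more items (h) | d, c = 0 to 0.3 | Power |
|---|---|---|
| correctly keyed | 0.35 | 0.82 |
| 2 | 0.21 to 0.30 | 0.34 to 0.68 |
| 3 | 0.14 to 0.25 | 0.14 to 0.48 |
| 4 | 0.07 to 0.15 | 0.04 to 0.16 |
| 5 | 0 | 0.017 (= alpha) |
| 6 | −0.07 to −0.15 | 0.04 to 0.16, wrong sign |

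Of the six food groups listed, only fruit and vegetables are plainly eat-more; drinks could go either way. The number of items per group is not given, so no row can be singled out.

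**The case against.** The strongest reply is that the article is a condensed account. It does not say that items stay unrecoded, and its scoring sentence is compatible with averaging items that have already been keyed. It also leaves out scoring detail for the two other primary instruments, and an item key is the sort of thing a full protocol or analysis plan holds. The intended direction is not in doubt either: the score is named as diet quality and the Background expects it to be higher with the intervention. The novelty of the questionnaire is openly listed among the limitations. The number of options is settled by the form already in use, and a comparison of groups is valid with four or five.

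Much of this stands. A reader might infer that there is no reverse scoring and that real dietary gains will cancel out. The article does not support that as fact: it is silent on recoding, and full cancellation needs exactly five eat-more items with equal shifts. A reader might also infer that the rule of one significant endpoint turns this fault into a false claim of success. It does not: if diet is unaffected, the unrecoded mean keeps its type I error of 0.0167. The calculated harm is lost power, or a reversed sign with six or more eat-more items, on one of three endpoints.

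What does not stand is that this is only omitted detail. The article fixes a coding and a rule, and the two followed as printed give an attenuated or wrong-signed result. It cites no scoring source that would override them. If items are in fact recoded, the published rule does not describe what will be done, and the direction of the drinks items stays open.

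**Conclusion.** The point holds in a limited form. The conflict between a 5-point scale and codes 0 to 3 is a plain contradiction and needs correction. The scoring rule, read as printed, lets opposite improvements offset each other in a co-primary endpoint. Whether this will happen in the analysis cannot be told from the article.

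If it does, the cost ranges from moderate attenuation (power 0.34 to 0.68 instead of 0.82 with two eat-more items) to no power beyond alpha with five and a reversed sign with six. These figures rest on an assumed item split, equal item shifts, correlation of 0 to 0.3 and a keyed effect of d = 0.35. They illustrate the range and do not forecast this trial. Quality of life and physical activity are not touched by it.

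**What to change.** Replace the scoring sentence with: *Items on foods to be eaten more often are reverse-coded so that a higher value always means better diet quality, then all items are averaged.* In addition:

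- list the reversed items and give the direction of each drinks item;
- correct either the number of scale points or the code range to match the questionnaire that was fielded;
- lock and date the key before any 3-month data are compared by arm. Item direction can be checked on baseline data pooled over both groups.

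The cost is a short amendment. According to Trial status, recruitment ended on 1 October 2019, this version dates from 13 November 2019 and follow-up runs to 1 April 2020, so baseline data are in hand. No new data collection or change in sample size is needed.
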